## 2.2.2 Safety and Clinical Use of Ceftriaxone in Humans

Ceftriaxone is generally well tolerated and severe adverse events have only rarely been reported. Over 100 million people have received ceftriaxone for the treatment of a variety of infections. Few patients have received ceftriaxone for more than six weeks. Ceftriaxone is not approved by the Food and Drug Administration (FDA) for treatment longer than 4-6 weeks. Toxicities of ceftriaxone are similar to those reported with other cephalosporins and include pseudomembranous colitis, super-infections, local pain on administration, phlebitis, fever,

pruritis, rashes, anorexia, nausea, vomiting, diarrhea, and abdominal pain. There is no evidence of teratogenicity in rodent study or in primates. There are no adequate studies in pregnant women.

Across many studies, the most frequently observed adverse events during treatment with ceftriaxone are hematological, including eosinophilia (6%), thrombocytosis (5.1%), leukopenia (2.1%), and thrombocytopenia (1%); however these adverse reactions have been reversed when drug administration was stopped [103]. Gastrointestinal adverse events during ceftriaxone therapy, primarily diarrhea (2.7%), are common. Ceftriaxone is also excreted via the bile leading to high biliary concentrations of the drug. Biliary adverse effects include the formation of biliary sludge leading to biliary obstruction, cholecystitis, choledocholithiasis, and pseudolithiasis. Prolonged use of ceftriaxone may result in overgrowth of nonsusceptible organisms. Neutropenia has been reported with ceftriaxone use. In one series, the mean time to develop neutropenia was 21 days (range 8-25 days). It was reversible upon discontinuation of the medication. The frequency of hypersensitivity skin reactions to ceftriaxone is between 1 and 3%; anaphylaxis is rare. The risk of anaphylaxis may be increased with a history of allergy to penicillin and is certainly increased with a history of allergic reaction to cephalosporin. Ceftriaxone is contraindicated in patients with known hypersensitivity to penicillins or cephalosporins. Nonconvulsive status epilepticus has been rarely reported with ceftriaxone use and is more common in patients with renal failure [104].

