Hospitalization for an elective procedure (including elective PEG tube/g-tube/feeding tube placement) or a routinely scheduled treatment is not an SAE by this criterion because a "procedure" or a "treatment" is not an untoward medical occurrence.
- Results in persistent or significant disability or incapacity  
This serious criterion applies if the "disability" caused by the reported AE results in a substantial disruption of the subjects' ability to carry out normal life functions.
- Results in congenital anomaly or birth defect in the offspring of the subject (whether the subject is male or female)

- Necessitates medical or surgical intervention to preclude permanent impairment of a body function or permanent damage to a body structure.

An event is considered "life-threatening" if it places the subject, in the view of the Investigator, at immediate risk of death from the reaction as it occurred; i.e., it does not include a reaction that, had it occurred in a more severe form, might have caused death.

Important medical events that may not result in death, are not life-threatening, or do not require hospitalization may also be considered SAEs when, based upon appropriate medical judgment, they may jeopardize the subject and may require medical or surgical intervention to prevent one of the outcomes listed in this definition. Examples of such medical events include blood dyscrasias or convulsions that do not result in inpatient hospitalization, or the development of drug dependency or drug abuse.

An inpatient hospital admission in the absence of a precipitating, treatment-emergent, clinical adverse event may meet criteria for "seriousness" but is not an adverse experience, and will therefore, not be considered an SAE. An example of this would include a social admission (subject admitted for other reasons than medical, e.g., lives far from the hospital, has no place to sleep).

An unexpected adverse event is any adverse event, the specificity or severity of which is not consistent with the current Investigator's Brochure.

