All serious adverse events (SAE) (including death and hospitalization), premature withdrawal, dosage changes and emergency treatment disclosures will be reported to the Coordination Center within one working day and SAE forms completed within 24 hours of their occurrence. The Medical Monitor and DSMB will review all SAE reports. Serious adverse events that occur during this study will be recorded in the subject's chart and on the CRF. All unexpected and related SAEs will be reported to the FDA, Health Canada as required, and to all sites by the Coordination Center. Death due to progression of disease, as expected in ALS, will not be reported in an expedited manner except in cases where the outcome of death is deemed related to study drug.

Sites will be instructed to submit these to their IRBs as well. Additionally, all SAEs will be reported to the FDA annually in the IND report. Any SAE that results in the study being put on hold at any site will be reported to all sites IRB, the NIH and the FDA. All unexpected and related SAEs will be reported to the FDA in an expedited manner, as required by FDA guidelines. Any adverse experiences will be followed for resolution.

There will be ongoing monitoring of non-serious Adverse Experiences through both the EDC system and on-site monitoring visits, to ensure adequate reporting of such events. The MGH Coordination Center will report all AEs to the FDA annually, and sites will be instructed to report AEs as required by their local IRBs. We have included in the Steering Committee two experts in infectious disease, one expert in nephrology, and one expert in gastroenterology, to advise us on how to minimize adverse events from the study drug.

---

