#### ***10.4.1 Evaluating and Recording of Adverse Events***

---

At each visit all adverse events that are observed, elicited by the Site Investigator, or reported by the subject will be recorded in the appropriate section of the Adverse Event log, entered into the EDC and evaluated by the Site Investigator.

Minimum information required for each AE includes type of event, duration (start and end dates), severity, seriousness, causality to study drug, action taken, and outcome.

The Site Investigator will grade the severity of AEs. The severity grading will be based on the unique clinical descriptions of severity for each AE in the CTCAE system, which follows this general guideline:

|         |                                  |
|---------|----------------------------------|
| Grade 1 | Mild AE                          |
| Grade 2 | Moderate AE                      |
| Grade 3 | Severe AE                        |
| Grade 4 | Life-threatening or disabling AE |
| Grade 5 | Death related to AE              |

---

The relationship of the AE to the study drug should be specified by the Site Investigator, using the following definitions:

1. Not Related: Concomitant illness, accident or event with no reasonable association with treatment.
2. Unlikely: The reaction has little or no temporal sequence from administration of the study drug, and/or a more likely alternative etiology exists.
3. Possibly Related: The reaction follows a reasonably temporal sequence from administration of the drug and follows a known response pattern to the suspected drug; the reaction could have been produced by the study drug or could have been produced by the volunteer's clinical state or by other modes of therapy administered to the volunteer.
4. Probably Related: The reaction follows a reasonable temporal sequence from administration of study drug; is confirmed by discontinuation of the study drug or by rechallenge; and cannot be reasonably explained by the known characteristics of the volunteer's clinical state.
5. Definitely Related: The reaction follows a reasonable temporal sequence from administration of study medication; that follows a known or expected response pattern to the study medication; and that is confirmed by improvement on stopping or reducing the dosage of the study medication, and reappearance of the reaction on repeated exposure.

---

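### A serious reaction that is new in kind, and either fatal or irreversible or also explicable by ALS, fits no related grade, so expedited reporting is not triggered

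*Combined protocol and SAP*

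**What the plan says.** Section 10.4 sets the trigger: "All unexpected and related SAEs will be reported to the FDA, Health Canada as required", and to all sites. The same section defines an unexpected event as "any adverse event, the specificity or severity of which is not consistent with the current" Investigator's Brochure. A death from progression is expedited only if it is judged related to study drug.

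Relatedness comes from Section 10.4.1, where the Site Investigator applies five definitions. The three that express a relationship are:

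- **Possibly Related:** "The reaction follows a reasonably temporal sequence from administration of the drug and follows a known response pattern to the suspected drug". The definition goes on to say that the drug, the clinical state or another therapy could have produced the reaction.
- **Probably Related:** reasonable timing, and the reaction "is confirmed by discontinuation of the study drug or by rechallenge; and cannot be reasonably explained by the known characteristics of the volunteer's clinical state".
- **Definitely Related:** reasonable timing, a reaction "that follows a known or expected response pattern to the study medication", and one "confirmed by improvement on stopping or reducing the dosage of the study medication, and reappearance of the reaction on repeated exposure".

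Unlikely covers weak timing or a more likely alternative cause. Not Related covers events with no reasonable association with treatment. The documents do not say which of the five grades count as related for the reporting rule.

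**The concern.** An expedited reporting rule exists mainly to carry news of reactions nobody has described before. Here the weakest related grade demands a pattern that is already known, while the next grade up does not. A reaction new in kind can be called related only through Probably Related, and that route closes if the patient dies, if the injury does not reverse, or if ALS could also account for the event.

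This matters more than usual in this trial. Section 2.2.2 states that "Few patients have received ceftriaxone for more than six weeks" and that the few published studies at 4 grams per day lasted 10 to 14 days. STAGES 1 and 2 added about 60 randomized subjects and a minimum of 20 weeks. STAGE 3 follows subjects for 12 to 36 months (Section 6.3.4). Section 10.4 also asks sites to watch for unexpected worsening of ALS. The documents describe no such known response to ceftriaxone, and the disease itself could always explain it, so that event falls in the gap unless ALS is judged the more likely cause, in which case it is Unlikely.

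**Working it through.** The plan gives no figure to reproduce; the check is of the definitions themselves. Take a reaction with reasonable timing and vary three things: whether its pattern is known, what stopping or re-exposure shows, and whether something else could explain it. That gives 2 × 3 × 3 = 18 combinations. The written conditions are:

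- Unlikely = weak timing, or a more likely alternative.
- Possibly = timing and known pattern.
- Probably = timing, and improvement on stopping or recurrence on rechallenge, and not explained by clinical state.
- Definitely = timing, known or expected pattern, improvement on stopping or reducing, and recurrence.

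For a reaction **new in kind** (3 × 3 = 9 combinations):

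| Stopping or re-exposure | Not otherwise explained | ALS could explain it | Another cause more likely |
|---|---|---|---|
| No information possible (fatal or irreversible) | no grade | no grade | Unlikely |
| Improves on stopping | Probably | no grade | Unlikely |
| Improves, and recurs on re-exposure | Probably | no grade | Unlikely |

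Four cells have no grade, three are Unlikely and two are Probably: 4 + 3 + 2 = 9. The four empty cells do not read as Not Related either, because the timing supplies a reasonable association. The top row contains no related grade at all.

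For a reaction of **known pattern**, Possibly Related is available in all nine combinations. That includes a known reaction that is unexpected only in severity, because the definition of unexpected covers severity as well as specificity.

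The trigger needs unexpected and related together. In the four empty cells the first condition can hold and the second cannot, so the rule as written is not met. These are counts of definitional cases, not of expected events.

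**The case against.** The strongest reply is that such events are not lost. Under Section 10.4 every SAE goes to the Coordination Center within one working day, is reviewed by the Medical Monitor and DSMB whatever its causality grade, and reaches the FDA in the annual report. Section 9.4.2 has the Medical Monitor follow SAEs in real time and lets that person notify the DSMB. Section 11.1 makes the PI responsible for reporting adverse events to the FDA, DSMB and site investigators, without a relatedness condition but also without a timeline. Section 10.4 also refers to FDA regulations and guidelines. All of this stands, and it limits the harm to the loss of expedited notice. None of it changes the definitions, and no section lets the Medical Monitor, DSMB or sponsor re-grade the site's causality assessment.

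It can also be said that a known response pattern is not defined by reference to the Brochure, so an event outside the Brochure may still follow a recognised cephalosporin pattern and be Possibly Related. That is right, and it is why the point is confined to reactions new in kind. An investigator might also treat the closing clause of Possibly Related as the working test, but the text joins timing and known pattern with a plain conjunction.

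A reader might infer several stronger things that the documents do not support:

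- **That the rule fails for all unexpected SAEs.** It does not. A new reversible reaction that clinical state does not explain can be Probably Related, and Sections 5.4.1 and 5.4.2 suspend drug for serious events, so information on stopping will often exist.
- **That the bar on rechallenge in Section 8 blocks grading of interstitial nephritis or tubular necrosis.** Both are known patterns, so Possibly Related is open, and Probably Related accepts discontinuation in place of rechallenge.
- **That the final safety analysis would omit these events.** Section 9.1.3 compares the occurrence of each adverse event by treatment group, with no relatedness filter.
- **That catheter bloodstream infections would be missed.** Section 7.3 lists them as expected, with a rate, so this trigger would not apply however they were graded. Separate causality fields for the catheter and ursodiol are a preference and do not bear on this gap.
- **That sites will settle on Unlikely.** Nothing in the documents shows what sites would do with an event that fits no definition.

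**Conclusion.** The point holds for a defined class: serious reactions with plausible timing that are new in kind and either fatal or irreversible, or reversible but also explicable by ALS. These are the four empty combinations out of nine for a new reaction. For them, the definitions followed as written yield no related grade, and expedited notice to the FDA, Health Canada and all sites is not triggered.

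The conclusion rests on a literal reading of Section 10.4.1, on related meaning one of the three positive grades (the natural reading, though nowhere stated), and on there being no second causality assessment outside these documents. The documents do not allow an estimate of how many such events would occur. The wording should be corrected because a rule followed exactly gives the wrong reporting result in a long-exposure trial; the existing SAE review keeps the consequence to delayed rather than absent notice to the FDA.

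**What to change.** Make three wording changes.

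1. In Section 10.4.1, delete the known-pattern condition from Possibly Related, leaving plausible timing and a reaction that the drug, the clinical state or another therapy could have produced.
2. In Probably Related, replace the mandatory confirmation with wording such as *supported by discontinuation or rechallenge information where available*.
3. In Section 10.4, state that possible, probable and definite all count as related for expedited reporting.

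Under the revised text all four empty combinations reach at least Possibly Related, and the two that were already Probably Related remain so. Definitely Related can stay as it is.

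The cost is protocol text, the matching guidance to sites, and somewhat more SAEs classed as related and expedited. One side effect needs a line of guidance: Possibly Related and Unlikely already overlap when a known reaction has a more likely alternative cause, and that overlap would extend to new reactions.

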## **11 HUMAN SUBJECTS**

### **11.1 Institutional Review Board (IRB) Review and Informed Consent**

The PI has obtained an IND from the FDA (IND 68,892), and has obtained approval from the Partners Human Research Committee (HRC, or Partners IRB) for the NCTU to serve as the Coordination Center for this trial. Each of the participating sites will also be required to obtain IRB approval of the protocol and consent form and send copies of these to the Coordination Center. The PI and Project Manager will review any alterations of the consent documents made by individual sites, to assure that all essential elements remain. Any subsequent modifications of the protocol or consent documents will be reviewed and approved by the MGH HRC and all site IRBs. Signed consent will be obtained from each subject. The consent form will describe the purpose of the study, the procedures to be followed, and the risks and benefits of participation. A copy of the consent form will be given to the subject, and this will be documented.

The PI and all key personnel involved in the study will have completed the Collaborative IRB training initiative, a mandatory tutorial on the responsible conduct of human subject research, or will have completed a comparable, institution-approved tutorial regarding the protection of human subjects. The NINDS has appointed a Data Safety Monitoring Board to review the study data for safety concerns. The PI will maintain minutes of the DSMB meetings and provide these to all the sites for submission to their IRBs. The PI will be responsible to report adverse events experienced by study subjects to the FDA, MGH IRB, the DSMB, NINDS and to all site investigators.

### **11.2 Subject Confidentiality**

Confidentiality will be maintained, as all subject research data will be coded with subject ID number and initials. The Coordination Center files will be kept in a secure, double-locked area. The electronic database used during the trial will be secure. To date no breach of our security barriers has occurred, and we actively maintain a high level of security to assess the confidentiality of our databases. Only key personnel in this proposal will have access to the data and the codes. Subject results will never be discussed in any form in the presence of other subjects in the study or with non-laboratory personnel. A subject will be referred to by his/her randomization ID number only. The primary risks of participating in the study are the potential adverse effects from the experimental intervention and the central venous catheter. The PI, Steering Committee, Medical Monitor and Data Safety and Monitoring Board will monitor safety and risks throughout the study. In the rare event that an investigator needs immediate knowledge of the subject's treatment assignment, the individual treatment assignment generated by the Biostatistics Center will be available.

### **11.3 Inclusion of Women**

The gender distribution for subjects with sporadic ALS is approximately 60% male and 40% female. The study goal is to recruit men and women with ALS in a 3:2 ratio. The MGH patient population includes 53% men and 47% women. Subjects at participating sites will be recruited from those site-specific areas and their surrounding communities. Special efforts will be employed to recruit female subjects. Advertising the study with several ALS and MND foundations will aid in the recruitment process, and in particular with the recruitment of female subjects.

The sites in the proposed study have demonstrated the ability to enroll females in prior NEALS and industry-sponsored studies. In the NEALS multi-center topiramate trial in ALS, 36% of the subjects were female. Similarly in the NEALS clinical trial of creatine in ALS and in the clinical trial of celebrex in ALS, 39% and 36% of the subjects were female, respectively. Each site has provided detailed enrollment goals and all sites documented ability to enroll 40% females. Copies of these documents are kept at the MGH Coordination Center. Based on this information, we do not anticipate difficulty enrolling the number of females for this study that represents the percentage of females with ALS in the total population.

### **11.4 Inclusion of Minorities**

ALS is a relatively rare disease and there is mixed data on its incidence in minority groups. Most epidemiologic studies of ALS have investigated homogeneous populations. One of the only mortality studies conducted within a large, multi-ethnic population by Annegers et al. (1991) found that age- and sex-adjusted mortality did not differ among ethnic groups [191]. Some studies suggest that ALS may be less frequent in non-white individuals. An incidence study in the state of Washington found rates in white males to be 1.8 per 100,000 compared to 0.74 per 100,000 per year for black males, although the difference was not statistically significant due to the small numbers of incident cases [8]. [name] recently determined the rates of ALS in whites, blacks and other racial groups in a cohort of US soldiers serving during the Gulf War I era. They concluded that the rate for ALS/MND in "Other racial groups" (mainly Hispanic) was significantly elevated compared to whites in this young, predominantly male cohort whereas the overall rate for blacks was 33% lower than the specific rates estimates [192].

Approximately 17% of the national population is of a non-white racial background. For the purposes of recruitment in this study we will assume a racial distribution similar to the overall US population. Ethnically, 12.5% of the national population is Hispanic or Latino (<http://www.census.gov>). Thus, the study goal is to enroll at least 12.5% of the subjects from this ethnic group. Approximately 13% of our nation's population is Black, 0.3% is Hawaiian/Pacific Islander, 4.2% is Asian, and approximately 1.5% is American Indian. Our goal is to enroll subjects with ALS that are representative of the nationwide demographics. The racial composition of MGH is 82% White, 3% Black, 1% Asian, and 12% unknown. The ethnic population of MGH is 3% Hispanic and 97% non-Hispanic. For geographical reasons, much of the local minority population does not have the MGH as its primary care facility in Boston.

To reach the recruitment goal, efforts will be focused on enrollment of individuals with ALS who are members of underrepresented minorities. Recruitment of members of minority groups will be closely monitored. Subjects will be recruited from the clinic population of the participating sites and through contact with support groups and healthcare providers from surrounding areas. IRB approval will be obtained for all planned letters, newsletters and web advertisements.

Potential study subjects will not be excluded from this study for reasons of race or gender and efforts will be made to enroll in representative numbers with respect to both gender and race. In particular, no racial discrimination will be made in subject enrollment. The participation of minority subjects will be actively encouraged throughout the study.

We will initiate different strategies to enhance minority recruitment and will include a section of these strategies in the Manual of Operations. The study PI will emphasize the significance of a balanced recruitment effort with each site investigator, as well as conduct reviews of recruitment rates. The study PI will contact sites with low minority enrollment and provide methods of improved recruitment.

